#### Phase 2—At-risk, in-care PLHIV

Participants will be randomized in a 1:1 ratio (*n* = 346 PLHIV/arm, *N* = 692 total), stratified by site, to comparison or intervention. We will use the *ralloc* function in Stata [53] to create computer-generated random permuted blocks of variable size between 2, 4, 6, and 8, with an equal allocation ratio between the two arms and stratified by study clinic. At the time of enrollment, a member of the study staff will randomize clients to the intervention or comparison arm based on this pre-determined randomization scheme. Due to the nature of the intervention, study participants, study staff, and health facility staff will not be masked to intervention assignment in Phase 2. For both phases, the study data analyst will not be masked to intervention assignment; however, study Principal Investigators and co-investigators will remain masked to individual participant intervention assignment throughout the study period. The study design is open label so unblinding will not occur.

### Assessments and data collection

#### Phase 1—Out-of-care PLHIV

Following enrollment HBCs will place a removable sticker on the outside of study participant-held medical record cards to identify clients as participants in the study. Next, study staff will register participants’ information into the study database, including registration of mobile money information (intervention participants only). Upon enrollment, the system will automatically transfer the first half of the incentive (11,250 TSH) via mobile money to those in the intervention arm. The HBC will explain that should they return to HIV care within 90 days of study enrollment, they will receive the second half (11,250 TSH) of the incentive (Fig. 2).

**Fig. 2 Fig2:**
[figure not shown]
Phase 1 study flow diagram

Health facility staff will monitor participants for return to HIV care by identifying the sticker on patient-held medical record cards among clients presenting for HIV care; in addition, study staff will conduct regular medical record data abstractions (Fig. 2) to assess for return to care. If return within 90 days is confirmed, entered clinical visit information will trigger the database to automatically send the second half of the incentive (11,250 TSH) to the participant. All payments will include extra funds for transaction fees, typically < $1. All participant data will be entered into the study Research Electronic Data Capture (REDCap) database, a secure web-based application used for data collection and management in clinical research.

Other study procedures for participants enrolled in phase 1 include:Baseline and endline survey (*n* = 640): Trained study staff will administer a structured baseline survey via phone to collect participant demographic, socioeconomic, and clinical information. The endline survey will be conducted either over the phone or at the health facility by trained study staff no earlier than 6 months post enrollment and only once linkage status has been confirmed.Medical record data abstraction: For participants who re-engage in care, study staff will retrospectively abstract data into study databases, including appointment attendance, HIV viral load, pharmacy dispensing, and current follow-up status.Viral load quantification: Viral load quantification will be conducted at intervals consistent with World Health Organization (WHO) and Tanzanian guidelines for monitoring HIV infection after re-engagement with care (SOC in all facilities). For those whose standard viral load draw schedule does not include a measurement at 6 months following study enrollment, a research viral load will be drawn. All collection, processing and analysis of blood samples will be conducted by local Tanzanian trained health workers and lab technicians. Specimens will be drawn by health facility personnel and transported to the hospital laboratory and/or regional hub, checked for quality, assigned barcodes, entered into the laboratory database, and centrifuged to retrieve plasma. Plasma will be stored and transported biweekly to testing laboratories, and results of testing will be made available within 2 days of sample arrival at the laboratory.Primary outcome measurement: We will assess the primary outcome of viral suppression 6 months after study enrollment. Those not on ART or with virologic failure (≥ 1000 copies/ml), or those who have died will be classified as not having the primary outcome. If there is no evidence of a documented HIV care visit in the participant’s medical record at any facility by 6 months after study enrollment, we will follow tracing procedures to confirm whether the individual is out of care, and if so, he/she will be classified as not in care, and not virally suppressed.

#### Phase 2—At-risk, in-care PLHIV

All participants will be enrolled in a clinic-operated mHealth system and asked to scan their fingerprint to register into the system (Fig. 3). Intervention participants will also provide their mobile money information for registration and will complete the first PKC session ideally on the day of enrollment. Participants in both arms will be asked to scan into the mHealth system using their fingerprint or their medical record identification number after attending all clinical visits following enrollment. Those attending PKC and the subset of control participants enrolled in EAC will also scan in after the conclusion of each session. For intervention participants only, receipt of each 22,500 TSH incentive is conditional upon confirmation of visit attendance and completion of each PKC session, which will be sent automatically through the mHealth system. Each payment will include extra funds for transaction fees. All participant data will be entered into the study REDCap database.

**Fig. 3 Fig3:**
[figure not shown]
Phase 2 study flow diagram

Other study procedures for participants enrolled in phase 2 of RKPK are as follows:Baseline, midline and endline surveys: Trained study staff will administer a baseline survey on the same day as enrollment, typically at the health facility. Approximately 6 and 12 months following enrollment, trained study staff will administer a structured midline and endline questionnaire, either over the phone or at the health facility.Viral load quantification: Viral load quantification will be conducted per SOC procedures by health facility staff and at intervals consistent with WHO and Tanzanian guidelines for monitoring HIV infection. All collection, processing, and analysis of blood samples will follow the same process as the samples collected in Phase 1. For those whose standard viral load draw schedule does not include a draw at 12 months following study enrollment, a research viral load will be drawn. Six-month viral load (study secondary outcome) data collection will follow a similar procedure.Enhanced tracing: At endline only, study staff will use enhanced routine tracing procedures according to national guidelines with additional robust tracing using the same “gold-standard” tracing methods (≥ 3 tracing attempts using multiple methods) to investigate all potentially LTFU clients, confirm “silent transfers” (those who transfer to new facilities without notification of the prior facility) and deaths, and refer clients to health facilities where missing plasma specimens can be collected for viral load quantification.Primary outcome measurement: Viral suppression will be assessed 12 months after enrollment. Those not on ART or with virologic failure or those who have died will be classified as not having the primary outcome. Among those with no evidence of an HIV care visit to any facility by 12 months after study enrollment, we will follow tracing procedures to confirm if they are out of care, and if so, he/she will be classified as not in care, and not virally suppressed.

#### Phase 3

Phase 3 will commence after the conclusion of phases 1 and 2 and will include IDIs with PLHIV who participated in phase 1 or 2, clinical staff at phase 1 and 2 health facilities, HBC providers at phase 1 health facilities, and government stakeholders such as Regional or District AIDS Control Coordinators and RMOs. We will also conduct surveys with health facility staff and HBCs at phase 1 and 2 health facilities.

This trial does not involve collecting biological specimens for storage.

### Power and sample size

Sample size for phase 1 was calculated to estimate the effectiveness of the incentive strategy for improving the proportion of PLHIV with suppression viral load at 6 months. We used estimates of 6-month viral suppression extrapolated from retention rates in our local studies [33, 37, 42] and viral suppression rates among PLHIV on ART [54] and an intracluster correlation coefficient of 0.01 [55]. We estimated that 72% of out-of-care PLHIV will return to care by 6 months after HBC contact alone, and in Tanzania, 92% of PLHIV on ART have viral suppression [54]. Thus, we estimate that 66% of PLHIV who are out of care at study initiation and in the comparison arm will have viral suppression at 6 months. With these estimates, we will have 80% power to detect a minimum detectable effect of 11 percentage points as an absolute increase in the percent of PLHIV with viral suppression at 6 months with 320 participants per arm (*n* = 640 total, 20 PLHIV/facility). This corresponds to 77% with viral suppression in the intervention arm, a clinically meaningful effect size similar to the pilot. Because attrition is part of the primary outcome, we will not inflate the sample size for LTFU.

Phase 2 will include 692 PLHIV. We estimate that 70% of PLHIV in the comparison group will achieve viral suppression at 12 months [33, 37]. Thus, we will have 80% power with a two-sided type I error of 0.05 to detect a relationship between the intervention and primary outcome if the proportion with viral suppression in the intervention group is at least 80% and 294 clients per group are enrolled. Adjusting for 15% LTFU, we will enroll 346 PLHIV per arm (*n* = 692 overall). Note that since we finalized the study protocol originally conducted our power calculations, the effectiveness of the newest first-line ART regimen containing dolutegravir (DTG) on durable viral suppression has become increasingly evident in several large cohort studies in sub-Saharan Africa. DTG-based regimens achieve higher rates of viral suppression compared to efavirenz-based regimens and are now recommended by WHO as the preferred HIV treatment option in all populations. Thus, we suspect that our original estimate of 70% viral suppression in the control group at 12 months may be low, although estimates of viral suppression among our subgroup of “high-risk” PLHIV on DTG-based regimens are unavailable; repeating our power calculations to account for a variety of possible ranges reveals that we are well powered for a variety of scenarios for what may occur in the control arm. For example, if viral suppression in the control arm were as high as 85% at 12 months, with our current sample size of 692, we retain at least 80% power to detect a 9 percentage-point difference between intervention and control participants. The expected number of participants proposed for phase 3 activities were based on previous studies where we have reached theme saturation emerging with interviews with PLHIV related to study implementation.

### Statistical analysis

All primary and secondary outcomes are pre-registered and included in the trial statistical analysis plan (ClinicalTrials.gov; Open Science Framework). For phase 1, our primary, intent-to-treat (ITT) analysis of 6-month viral suppression will be a cluster-based permutation test on the individual-level outcome data, which accounts for clustering within the health facility. Multiple imputation will be used for all missing viral load data for those who re-linked to care but do not have a viral load quantified in our pre-specified assessment window. We will also construct a regression model to derive an RD with a 95% CI. For phase 2, the primary ITT analysis of 12-month viral suppression will be examined by study group using a generalized estimating equation that accounts for clustering within facility and adjusted for health facility, and will be expressed as a RD and 95% CI. For both phase 1 and 2 primary analyses, multiple imputation will be used for outcomes with > 5% missing and for covariates if 5% or more records have missing covariates and would therefore be excluded from adjusted analyses.

We will follow similar procedures as our primary outcome analysis described above for all secondary outcome proportions (Table 2: Secondary outcomes). For both phases 1 and 2, secondary analyses include assessing primary outcome data in complete case analyses that do not impute for missing outcome or covariate data. We will assess for heterogeneity in primary and secondary outcomes by facility characteristics, such as geographic region and facility size, and client characteristics, including sex, age, viral suppression at enrollment, and time out of HIV care (phase 1 only). Additionally, we will employ causal inference methods to estimate per-protocol estimands for phase 1 and 2 primary outcomes. Other trial outcomes include data from participant surveys and include assessments of food security, physical, sexual, and mental health, violence, participation in the labor force, household characteristics, and cash incentive usage (Table 2: Survey outcomes).

**Table 2 Tab2:** Trial secondary outcomes and survey outcomes

Outcome	Phase 1	Phase 2
*Secondary outcomes*		
Proportion with HIV viral suppression 12 months after enrollment	X	
Proportion with durable HIV viral suppression 12 months after enrollment	X	X
Appointment attendance	X	X
Cumulative incidence of mortality at 12 months after enrollment	X	X
Cumulative incidence of viral suppression at 12 months after enrollment	X	X
Proportion retained in HIV care at 6 months after enrollment	X	X
Proportion retained in HIV care at 12 months after enrollment	X	X
Time to re-linkage to HIV care	X	
Cumulative incidence of re-linkage to HIV care 12 months after enrollment	X	
*Survey outcomes*		
Food security	X	X
Physical, sexual, mental health	X	X
Intimate partner violence/non-partner violence	X	X
Participation in the labor force	X	X
Spending and welfare	X	X
Incentive usage	X	X

Phase 3 provider survey data will be summarized using descriptive statistics. Qualitative data analysis will be conducted using Dedoose software and will be based on the CFIR domains which will inform the initial coding framework. Qualitative data analysis will follow an open-coding approach [56, 57] and will be based on research questions and study aims. Concepts will be grouped into themes by CFIR domain and will be summarized in an analytic theme matrix.

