## Methods/design

### Design

The overall objective of RKPK is to evaluate two implementation strategies of an economic incentive intervention for supporting PLHIV struggling with continuity of care in Tanzania (Fig. 1). The study includes three distinct phases:Phase 1 is a cluster randomized trial of PLHIV disengaged from HIV care in which 32 health facilities will be randomized in a 1:1 ratio to standard of care (SOC) or the economic incentive intervention. The pre-registered primary endpoint (ClinicalTrials: NCT05248100) is viral load suppression at 6 months, defined as the proportion of PLHIV on ART and with suppressed HIV viral load (< 1000 copies/ml) 6 months after enrollment. The intervention implementation model is a home visit by an HBC provider (SOC in Tanzania mandates that PLHIV who are identified as LTFU from an HIV clinic or who miss a regularly scheduled appointment are initially be traced and contacted by an HBC provider), plus a one-time incentive for returning to care.Phase 2 is a 2-armed, parallel 1:1 individually randomized controlled trial conducted at two high-volume health facilities to evaluate the effectiveness of a short-term economic incentive program offered to in-care PLHIV who are predicted to be at risk of disengaging from HIV care using a machine learning algorithm developed using routinely collected medical and pharmacy electronic medical record (EMR) data from the parent regions. The pre-registered primary outcome is the proportion of PLHIV on ART and with suppressed HIV viral load (< 1000 copies/ml) 12 months after enrollment (ClinicalTrials: NCT05373095). The intervention implementation strategy includes up to 3 monthly incentives conditional upon visit attendance and attendance at “Pamoja Kundini” counseling (PKC) sessions, adapted from SOC enhanced adherence counselling (EAC) sessions designed to address the challenges of long-term HIV care engagement with respect and empathy.Phase 3 will explore implementation challenges and successes using a mixed methods design. We will conduct surveys and in-depth interviews (IDIs) to assess barriers and facilitators to phase 1 and 2 implementation for both groups of PLHIV and from multiple stakeholder perspectives including health facility staff, HBCs, and government staff. Guided by the Consolidated Framework for Implementation Research (CFIR) [46] we will examine individual (perceptions, motivations), intervention (barriers, facilitators), and contextual factors (management, policies) that influence intervention effectiveness.

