### Health facility eligibility and recruitment

For phase 1, we will work with the Regional Medical Officers (RMOs) in Geita and Kagera Regions (Lake Zone) to generate a list of HIV care facilities currently using an EMR database and that had at least 750 PLHIV on ART in any quarter of 2021. We will proceed with a two-part facility selection process: separately by region, we will use ArcGIS geographic information system software to randomly select a set of up to 25 facilities ≥ 15 km from any other facility in the list. From this list, we will randomly select 16 facilities per region for study inclusion. Phase 2 includes two purposively selected large facilities in Geita Region.

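### The Phase 2 primary GEE takes facility as its clustering unit with only two facilities; the usual facility-level sandwich variance cannot then give both the planned 5% error and 80% power

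*Protocol article*

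**What the plan says.** The Design section describes Phase 2 as a "2-armed, parallel 1:1 individually randomized controlled trial conducted at two high-volume health facilities". The section on facility eligibility confirms the number: "Phase 2 includes two purposively selected large facilities in Geita Region". Under Randomization and masking, permuted blocks are generated "with an equal allocation ratio between the two arms and stratified by study clinic".

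The Statistical analysis section sets the primary intention-to-treat comparison of 12-month viral suppression "using a generalized estimating equation that accounts for clustering within facility and adjusted for health facility", reported as a risk difference with a 95% interval. Facility is therefore both the clustering unit and a covariate. The section plans multiple imputation when more than 5% of outcomes are missing, and similar procedures for the secondary proportions. It does not give the variance estimator, working correlation, small-sample correction or reference distribution.

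The Power and sample size section plans on "80% power with a two-sided type I error of 0.05 to detect a relationship between the intervention and primary outcome". On the control rate it says: "We estimate that 70% of PLHIV in the comparison group will achieve viral suppression at 12 months". The intervention rate is 80%, with 294 per arm raised to 346 for 15% loss to follow-up. No intracluster correlation enters the Phase 2 calculation, whereas Phase 1 uses 0.01.

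**The concern.** A facility-level sandwich variance estimates uncertainty from how cluster scores vary, so it needs many clusters. Here there are two. With a facility term in the model the two treatment scores sum to zero, so they carry one independent piece of information. The variance becomes a single squared number and is usually much too small.

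The design does not call for this variance. Participants are randomised within facility, and the facility term already removes the difference in suppression between the two sites.

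At stake are the confirmatory test and interval for Phase 2, and the secondary proportions that follow the same approach. Under some permissible readings of the sentence, an ineffective programme would often be declared effective with an interval far too narrow.

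**Working it through.** **1. Reproduce the plan's sample size.** Inputs from Power and sample size: 70% versus 80%, two-sided 0.05, 80% power, 15% loss.

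n = [1.96·√(2·0.75·0.25) + 0.8416·√(0.70·0.30 + 0.80·0.20)]² / 0.10² = (1.2002 + 0.5119)² / 0.01 ≈ 293.2, so 294 per arm. Then 294 / 0.85 = 345.9, so 346. Both figures reproduce exactly as a two-proportion calculation with independent participants.

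**2. The facility-clustered sandwich with two facilities.** Let d1 and d2 be the within-facility risk differences and w1 and w2 the facility shares of the sample, with 1:1 allocation in each. Under an identity link with a facility term:

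- estimate = w1·d1 + w2·d2
- uncorrected sandwich SE = √2·w1·w2·|d1 − d2|

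With equal facilities the SE is |d1 − d2|/(2√2), so the Wald statistic is √2·(d1 + d2)/|d1 − d2|. Under the null, d1 + d2 and d1 − d2 are approximately independent normals with equal variance. The statistic is therefore √2 times a Cauchy variable (in absolute value).

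- Uncorrected, normal reference: 1 − (2/π)·atan(1.96/√2) = 39.8%. Coverage of the 95% interval is the complement, about 60%.
- With G/(G−1) = 2, the SE grows by √2 and the statistic is a plain Cauchy: 1 − (2/π)·atan(1.96) = 30.0%.
- With G/(G−1) and t on 1 df (critical value 12.706): 5.0%.

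**3. Simulation, N = 692, complete data.** Closed-form simulation used 200,000 trials per setting, with control rates of 65% to 90%.

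| Variance and reference | Type I error, equal facilities | Power, 70% vs 80% |
|---|---|---|
| Facility sandwich, uncorrected, normal | 39–40% | not meaningful at this size |
| Facility sandwich, G/(G−1), normal | 30–31% | not meaningful at this size |
| Facility sandwich, G/(G−1), t on 1 df | 5–6% | 19% |
| Model-based | 5.0–5.1% | 86% |
| Participant-level robust, facility as stratum | 5.0–5.2% | 86% |

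Fitted GEEs (identity and logit links; independence and exchangeable working correlation; 500 to 1,500 trials each) gave 39–41% with the robust SE and 4–5% with the model-based SE.

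The article does not give the facility split. Under assumed splits the uncorrected sandwich gave 37–39% at 440/252 and 45–50% at 520/172.

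**4. With multiple imputation.** Between-imputation variance does not depend on the two-facility contrast, so it dilutes the problem. The check used equal facilities, 70% suppression, 20 imputations within arm and facility, Rubin's rules and the uncorrected sandwich. Type I error was about 27% at 5% missing, 21% at 10% and 17% at 15%, against 39% with none missing. The missing fractions are assumptions. Participants confirmed out of care or dead count as not suppressed, so the fraction may be small. At or below 5% the plan does not impute and the complete-data figure applies.

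**The case against.** The strongest reply is that the article names a GEE and not a sandwich. The variance estimator and any finite-cluster correction are details that an analysis plan commonly carries; one exists and is not shown. The same GEE with a model-based SE holds about 5%. This stands against any unconditional claim: a reader might infer that the plan has a 40% false-positive rate, and the article does not support that. It supports a range that depends on an unstated choice. Multiple imputation would also bring the figure below 40% once it applies.

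The reply does not dispose of the point. Facility as clustering unit is a stated choice, not an omitted detail. With facility already a fixed covariate, the model-based route adds no clustering correction, so the facility-clustered sandwich is the natural way to carry out the sentence.

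A reader might also infer that Phase 2 has no clustering of any kind. That goes too far: intervention participants attend three sessions with facility counsellors, so outcomes could correlate by counsellor in one arm. A two-facility sandwich would not correct this, and neither does a participant-level variance.

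**Conclusion.** The point holds conditionally. If the Phase 2 GEE uses a facility-level sandwich variance, no version examined delivers both the two-sided 5% error and the 80% power that the plan states. Type I error is about 40% uncorrected or 30% with G/(G−1) (normal reference, complete data, equal facilities). The only correction that restores about 5% leaves about 19% power. With imputation at an assumed 5–15% missing, the uncorrected version still gives about 17–27%. If a model-based SE is used, the test is sound, but the clustering clause then does no work.

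Either way, the analysis sentence names the facility as the independent unit while the sample size takes the participant. It should be corrected before Phase 2 analysis is fixed.

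**What to change.** For the Phase 2 primary outcome and secondary proportions, delete the clause on within-facility clustering. Keep facility as a fixed stratum, matching the stratified randomisation, and name a participant-level variance. Acceptable forms include an identity-link model with a facility term and individual-level robust or model-based standard errors, or a Mantel-Haenszel risk difference stratified by facility. State that this assumes no material correlation by counsellor.

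The cost is one sentence in the protocol and the matching text in the analysis plan. Sample size and data collection do not change, and the Trial status section lists Phase 2 as not yet recruiting.

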#### Phase 2—At-risk, in-care PLHIV

Eligible PLHIV are those: (1) currently on ART and with a valid viral load result in the last 6 months (indicating current or recent care engagement); (2) not currently enrolled EAC in nor starting EAC sessions within 1 week; (3) ≥ 18 years; (4) with ownership of a phone/with consistent phone access; (5) living in Geita Region and intending to receive care at a study facility for the next 12 months, and (6) classified as “high-risk” for disengagement from HIV care using our machine learning algorithm. We will consider for inclusion in the algorithm routinely collected medical and pharmacy EMR data that partially explain observed information about viral suppression and/or retention, including patterns of viral load, adherence, and visit attendance. We will then develop a predictive model using data from the participating regions to identify PLHIV who are at high-risk for disengaging from care, having high viral load, or death. Using a facility-generated dataset of clients currently accessing care at the facility, our study team will create a list of potentially “high-risk” clients via our machine learning model, which will then be used by health facility staff to recruit and enroll clients for study participation.

#### Phase 3

We will recruit and invite a subset of PLHIV who participated in phase 1 or 2 for participation in IDIs and will purposively select health facility staff and HBCs who participated in study implementation for participation in surveys and IDIs (Table 1). Consistent with our goal to optimize intervention strategies for wider scale-up, if found effective, we will recruit key government stakeholders identified as having authority over health-related activities in study communities for participation in IDIs.

**Table 1 Tab1:** Phase 3 Stakeholder Groups and Data Collection Activities Linked to Domains in the Consolidated Framework for Implementation Research (CFIR, Damschroder, 2009). All data collection activities will occur after conclusion of enrollment for phase 1 or phase 2

Stakeholder group	Data collection approach	CFIR domain(s)
Health facility staff (directors, head nurses, in-charge physicians, and other facility staff)	Surveys (*n* = 64) In-depth interviews (~ 20)	• Inner setting • Intervention characteristics • Characteristics of individuals • Process

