#### Phase 2—At-risk, in-care PLHIV

Participants randomized to the comparison arm will receive SOC HIV clinical services according to Tanzania’s National Guidelines for the Management of HIV. Viral suppression rates are expected to be high, but a small subset of participants will have detectable viral load (≥ 1000 copies/ml) during the study period and will therefore meet health facility criteria for EAC. SOC EAC includes the standard provision of three, once-monthly, 60-min individual, counselling sessions with a trained counselor on the clinical staff. EAC sessions focus on the meaning of viral loads and supportive, non-judgmental strategies to bolster adherence and visit attendance.

Participants randomized to the intervention arm will receive the same standard HIV care services plus the offer of up to three 22,500 TSH incentives if visit attendance and attendance at each of the three adapted PKC sessions is confirmed using a clinic-operated mHealth system PKC, which is adapted from SOC EAC, is viral suppression “agnostic,” focuses on *potential* barriers to adherence, and is intended to address the challenges of long-term HIV care engagement with respect and empathy. It was co-created with experienced “HIV counselors” and mental health professionals/psychologists at the study facilities with input from PLHIV who are currently retained in care. The resulting PKC guide covers many of the components of EAC (e.g., stigma, mental health, coping with HIV, practical tips for success) but also includes motivations/barriers to staying in HIV care, status disclosure, treatment supporter check-ins, and long-term health goals and planning. In the three 1:1 sessions, participants will work with the trained health facility counselor to navigate barriers and create a plan to stay in care.

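### The Phase 2 primary model names health facility as its only adjuster; adding baseline viral load, and the risk score if it is stored, would be a free but small-to-moderate gain in precision

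*Protocol article*

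**What the plan says.** Statistical analysis: the Phase 2 intent-to-treat comparison of 12-month suppression uses a GEE that "accounts for clustering within facility and adjusted for health facility, and will be expressed as a RD and 95% CI". Facility is the only adjuster named. The same paragraph, speaking of both phases' primary analyses, provides for multiple imputation "for covariates if 5% or more records have missing covariates and would therefore be excluded from adjusted analyses", without listing those covariates. The next paragraph names "viral suppression at enrollment" as a factor for heterogeneity analyses, and refers readers to a separate SAP for outcomes.

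Participant eligibility and recruitment, Phase 2: entrants must be "currently on ART and with a valid viral load result in the last 6 months", must be "not currently enrolled EAC in nor starting EAC sessions within 1 week", and must be classified as high-risk "for disengagement from HIV care using our machine learning algorithm". The model behind the classification is meant to "identify PLHIV who are at high-risk for disengaging from care, having high viral load, or death".

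Study arms, Phase 2: comparison-arm participants whose viral load is 1000 copies/ml or more during the study "will therefore meet health facility criteria for EAC" (enhanced adherence counselling).

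Power and sample size: 70% versus 80%, two-sided 0.05, 80% power, 294 per arm, raised to 346 per arm (692 in total) for 15% loss to follow-up.

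**The concern.** The Phase 2 primary outcome fails through three routes: not being on ART or in care, virologic failure, or death. The algorithm targets essentially those events, and a recent viral load bears directly on one of them. Both come from the eligibility process, so at least the viral load is in hand for everyone before randomisation. It is already earmarked, as suppression status, for subgroup work. The sentence defining the primary estimate names neither.

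In a randomised trial, adjusting for a prognostic baseline variable generally narrows the interval around the RD. It also guards against chance imbalance, and here randomisation is stratified by site only. What is at stake is precision, not bias. It matters somewhat more because the article itself suspects that its 70% control rate is too low, and a higher rate leaves less room for an effect.

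**Working it through.** **Inputs from the article.** Control 70%, intervention 80%, two-sided alpha 0.05, power 80%, 294 per arm, 15% loss, 346 per arm (Power and sample size). 1:1 allocation stratified by site (Randomization and masking).

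**Input not in the article.** R2, the share of outcome variance explained by the added covariates beyond arm and facility. It is assumed, with a range of 0.01 to 0.10.

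**Step 1: reproduce the stated sample size.** With pooled variance and no continuity correction:

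n = [1.96·√(2·0.75·0.25) + 0.8416·√(0.7·0.3 + 0.8·0.2)]² / 0.10² = (1.2002 + 0.5119)² / 0.01 ≈ 293.2, rounded up to 294.

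294 / (1 − 0.15) = 345.9, rounded up to 346.

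Both figures match exactly with no covariate gain built in. Power at 294 per arm is 80.1%.

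**Step 2: effect of adjustment.** The variance of the RD is multiplied by about (1 − R2), so:

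- effective n = n / (1 − R2)
- power = Φ{[0.10·√(effective n) − 1.96·√0.375] / √0.37}
- 95% CI half-width = 1.96·√[(0.37 / n)·(1 − R2)]

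| R2 (assumed) | Effective n at 294/arm | Power, 294/arm | n/arm for 80% power | CI half-width, 294/arm (points) | Power, 346/arm |
|---|---|---|---|---|---|
| 0 | 294.0 | 80.1% | 294 | 6.95 | 86.1% |
| 0.01 | 297.0 | 80.5% | 292 | 6.92 | 86.4% |
| 0.02 | 300.0 | 80.9% | 289 | 6.88 | 86.8% |
| 0.05 | 309.5 | 82.1% | 280 | 6.78 | 87.8% |
| 0.10 | 326.7 | 84.1% | 265 | 6.60 | 89.4% |

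**Step 3: what R2 could baseline suppression status supply?** Let q be the share suppressed at entry, a and b the 12-month suppression rates in those suppressed and unsuppressed at entry, and m = q·a + (1 − q)·b. Then R2 = q(1 − q)(a − b)² / [m(1 − m)]. All rates are assumed.

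- q = 95%, a = 75%, b = 50%: m = 0.7375, R2 = 0.0475·0.0625 / 0.1936 = 0.015.
- q = 95%, a = 80%, b = 40%: m = 0.78, R2 = 0.0475·0.16 / 0.1716 = 0.044.
- q = 98%, same two pairs: R2 = 0.006 and 0.019.
- q = 80% to 90%, same two pairs: R2 = 0.03 to 0.13.

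The first three lines fit the eligibility rules better. A result of 1000 copies/ml or more leads to EAC, and people in EAC or about to start it are excluded.

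**Step 4: what could a continuous risk score supply?** Take a normally distributed score and 75% overall suppression. An AUC within the enrolled group of 0.60, 0.65 or 0.70 (assumed) gives R2 of about 0.02, 0.05 or 0.10. If viral load patterns enter the algorithm, as the eligibility text allows, the two covariates overlap and their R2 values do not add up.

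**The case against.** The strongest reply is that nothing here is wrong. The model adjusts for the factor on which randomisation was stratified, the sample size reproduces without further adjustment, and a full covariate list is something an article may leave to the SAP. This stands as regards validity and power, and it limits the point to an improvement of a stated method.

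A reader might infer that the primary analysis ignores all other baseline data. The text does not support that. Its imputation rule anticipates missing covariates in the primary analyses. Facility, as a randomisation stratum, would hardly be missing, so other covariates may be listed in the SAP. What can be said is that the article names none.

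A reader might also expect a large gain from baseline viral load. The EAC exclusion argues against that, because suppression status should vary little at entry. The exclusion is not complete, though: the rule asks for a valid result, not a suppressed one, and does not cover people who have finished EAC or will start it later. The log10 value may also carry information below the threshold.

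The score is the least certain part. The article states a high-risk class, which is the same for every participant. It says that a list is generated and passed on for recruitment, not that a continuous score is kept. Selecting on the score also narrows its range among those enrolled.

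Finally, a reader might conclude that Phase 2 is underpowered without adjustment. The documents do not show this. For the article's own alternative, 85% control and a 9-point difference, unadjusted power is 94.7% at 294 per arm and 97.3% at 346.

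**Conclusion.** The point holds as an efficiency improvement. Facility is the only adjuster named, every participant has a recent viral load at entry, and all are classified by an algorithm directed at the components of outcome failure. Not using such data gives up some precision for no benefit.

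The likely size is small to moderate: 0.4 to 4.0 power points at 294 per arm, and at most 0.35 points off the CI half-width, over an assumed R2 of 0.01 to 0.10. Suppression status alone would give R2 of about 0.01 to 0.04 if 95% to 98% are suppressed at entry. The upper part of the range depends on a retained, still-discriminating continuous score, or on more baseline viraemia than the eligibility rules suggest. No R2 appears in the documents, so these figures show scale and are not predictions. Type I error, validity and the stated 294 and 346 per arm are not affected.

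**What to change.** Pre-specify the Phase 2 primary result as a marginal (standardised) RD with 95% CI from a model containing:

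- arm;
- health facility;
- baseline viral load, preferably as log10 copies/ml because few participants should be at or above 1000, with a stated coding for results below the assay limit;
- the continuous algorithm score at the time of listing, if it is retained.

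Standardisation keeps the estimand the same marginal RD that the article already promises. Keep the facility-only RD as a sensitivity analysis. If the SAP already lists these covariates, say so in the protocol text, which would also explain what the missing-covariate rule refers to.

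The cost is wording. Viral load is already collected for eligibility. The score needs only to be saved with the recruitment list, if that is not already done. The article reports Phase 2 as not yet recruiting, so at that point the change could be made before any outcome data existed.
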